#### Secondary outcomes

2.14.2

Current, mean, and maximum headache intensity will be tested using two-way repeated measures ANOVA or the non-parametric alternative, in alignment with the analysis of the main outcome. The headache incidence and the use of on-demand pain medication will be used to calculate odds ratios to compare the odds of developing headaches or using pain medication up until 72 h after LP between the OPT and SOC groups. Differences in expectations regarding the extent of unwanted side effects, state anxiety, perceived warmth and competence of the physician, and satisfaction with the procedure will be assessed using independent t-tests or Wilcoxon rank-sum tests (in the case of non-parametric data). For confirmatory analyses of group differences in the secondary outcomes, an alpha level of 0.05 after comparison for multiple testing using the Bonferroni–Holm procedure will be regarded as statistically significant.

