#### State anxiety

2.11.2

State anxiety was assessed immediately after ICP (t2) by calculating the total score from the 20 items of the state anxiety subscale from the State–Trait Anxiety Inventory (STAI) (Ferreira and Murray, 1983).

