#### Survey time point 1 (t1)—baseline assessments

2.12.1

After enrollment, patients completed questionnaires to assess trait anxiety and depression [trait subscale of the State–Trait Anxiety and Depression Inventory, STADI-Trait (Laux et al., 2013)] and the baseline presence and severity of the following symptoms during the past 7 days: nausea, headache, vertigo, back pain, changes of vision, hearing or sensation, and photo- or phonophobia symptoms [modified General Assessment of Side Effects, GASE (Rief et al., 2011)]. Current headache intensity was assessed on a numerical rating scale (NRS) from 0 to 10. Basic demographic and biometric characteristics were recorded (age, sex, education, height and weight, blood pressure, and heart rate at admission) as well as current medication, days with alcohol consumption per month, and nicotine consumption (in pack years). The reason for admission was stated freely (e.g., neurological symptoms or recent findings requiring further investigation). The presence of a suspected or known underlying neurological diagnosis was also recorded. Illness perception was assessed using the following three items from the Brief Illness Perception Questionnaire (modified B-IPQ) (Broadbent et al., 2006): experience of symptoms, impact on daily life, and degree of concern. Information was further obtained on patients’ prior experiences with similar procedures, that is, epidural or spinal anesthesia, and their satisfaction with these procedures. Finally, the reason for admission, indication for LP, and suspected diagnosis as given by the treating ward physicians were noted.

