#### Exploratory analyses

2.14.3

The number needed to treat with optimized communication to prevent a certain level of headache-related impairment can be assessed exploratively (e.g., greater than 2 out of 10). Analyzing differences in reported side effects other than headache (assessed in the modified GASE questionnaire) allows us to test whether the optimized communication strategy influenced a wider range of side effect symptoms. Furthermore, the dataset lends itself to the exploration of associations between the study’s outcomes and demographic as well as baseline psychometric characteristics (e.g., age, sex, trait anxiety, trait depression), as their contribution to the outcomes can be controlled for and potential influences between outcomes, that is, through modulation, can be explored. The importance of perceived warmth and empathy of the physician—largely influenced by non-verbal communication—will be examined by analyzing the variance in side effect outcomes explained by patients’ ratings of the physician’s warmth, also probing for a potential modulatory influence on the group effect. The exploratory analyses are intended to make novel discoveries and help generate new hypotheses regarding biopsychosocial mechanisms through which the optimized communication might act or regarding predictive factors that might identify patients who benefit most from our optimized communication protocol.

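### The confirmatory test of state anxiety ignores the trait anxiety score already collected at baseline, which gives up precision without making the test invalid

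*Protocol article*

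**What the plan says.** Section 2.11.2 defines the outcome: "State anxiety was assessed immediately after ICP (t2) by calculating the total score from the 20 items" of the STAI state subscale. Table 2 and section 2.12.1 list no state anxiety measurement at t1, so the outcome has no baseline value of its own.

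Section 2.12.1 does record a closely related measure before the intervention: "patients completed questionnaires to assess trait anxiety and depression" (STADI-Trait).

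Section 2.14.2 fixes the test: "state anxiety, perceived warmth and competence of the physician, and satisfaction with the procedure will be assessed using independent t-tests or Wilcoxon rank-sum tests". It names no covariate. The same section gives the test confirmatory status: "For confirmatory analyses of group differences in the secondary outcomes, an alpha level of 0.05" applies after Bonferroni–Holm correction.

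Trait anxiety appears in the analysis plan only in section 2.14.3, among "baseline psychometric characteristics (e.g., age, sex, trait anxiety, trait depression), as their contribution to the outcomes can be controlled for". That section describes its analyses as hypothesis-generating.

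Section 2.7 sets 40 patients per group and assigns each block of 10 consecutively enrolled patients as a whole to one group. It describes no stratification by anxiety.

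**The concern.** State anxiety matters to the argument of the trial. The Introduction says that negative communication raises anxiety, and the Discussion says that anxiety feeds nocebo effects. Section 2.11 gives the secondary outcomes the task of supporting the intervention effect, and this one must pass a Holm-corrected family.

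Patients who are anxious by disposition can be expected to score higher on state anxiety whatever is said to them. A two-sample test leaves that variation in the error term, and its point estimate carries any observed difference in trait anxiety between the arms. A covariate that is measured before the intervention and is already in the dataset can remove part of that noise and correct the estimate for the imbalance seen. Recruitment was limited by staff resources, so a larger sample was not an available route to precision. The article names the test, so this is a question about a stated choice and not about detail left to an unseen analysis plan.

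**Working it through.** **The plan's own figure.** The article gives no power for state anxiety. Its only power statement (section 2.7) is for the group-by-time interaction on the primary outcome: f = 0.16 at power 0.90. With N = 80, 3 time points, an assumed correlation of 0.5 between repeated measures and sphericity, λ = f²·N·3/(1 − 0.5) = 0.0256 × 240/0.5 = 12.29. On 2 and 156 degrees of freedom at alpha 0.05, power is 0.885. The smallest f with power 0.90 is 0.164, which rounds to 0.16, so the figure reproduces. It says nothing about state anxiety.

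**Inputs.** From the article: 40 per arm and alpha 0.05 after Holm. Assumed: a two-sided test, a standardised difference d = 0.5, a trait-state correlation r over a range, and independent patients.

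**Precision.** Adjusting for trait anxiety multiplies the variance of the group difference by 1 − r², so the effective standardised difference is d/√(1 − r²). Power comes from the noncentral t distribution. The last column is 80/(1 − r²).

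| r | variance factor | power, alpha 0.05 | power, alpha 0.005 | unadjusted N that matches 80 adjusted |
|---|---|---|---|---|
| no adjustment | 1 | 0.60 | 0.27 | 80 |
| 0.3 | 0.91 | 0.64 | 0.30 | 88 |
| 0.5 | 0.75 | 0.72 | 0.39 | 107 |
| 0.6 | 0.64 | 0.79 | 0.47 | 125 |

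Alpha 0.005 is the first Holm step, 0.05/10. It counts ten tests: expectation, state anxiety, headache incidence, current, mean and maximum intensity, pain medication, warmth, competence and satisfaction. Allowing for the degree of freedom spent on the covariate lowers the adjusted powers at alpha 0.05 slightly, to 0.633, 0.717 and 0.783.

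The difference detectable with 80% power at alpha 0.05 is 0.63 SD unadjusted and 0.63 × √0.75 = 0.55 SD at r = 0.5.

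**Sensitivity to the assumptions.** At r = 0.2 and d = 0.5, power at alpha 0.05 moves only from 0.598 to 0.616. At d = 0.8 and r = 0.5 it moves from 0.942 to 0.983 at alpha 0.05, but from 0.752 to 0.889 at alpha 0.005.

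**Observed imbalance.** Under independence the standardised difference in mean trait anxiety has standard error √(2/40) = 0.224. A gap above 0.3 SD in either direction therefore has probability 2·P(Z > 0.3/0.224) = 0.18. Given a gap D, the unadjusted state-anxiety difference shifts by r·D. For D = 0.3 that is 0.09, 0.15 and 0.18 SD at r = 0.3, 0.5 and 0.6.

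**Validity over randomisations.** Given D, the null difference is approximately normal with mean r·D and variance 0.224²·(1 − r²). At r = 0.5 the conditional rejection rate is 0.13 when D = 1.96 × 0.224 = 0.44, and 0.02 when D = 0. In 20,000 simulated trials with individual randomisation, the overall type I error at r = 0.5 was 0.053 for both the t-test and the adjusted model.

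**Block allocation.** If patients within a block of 10 resemble each other, variances grow by 1 + 9·ICC. At an assumed ICC of 0.02 or 0.05 the factor is 1.18 or 1.45. The standard error of the trait imbalance becomes 0.243 or 0.269, and the chance of a gap above 0.3 SD becomes 22% or 27%. Any such similarity in state anxiety also lowers the true power below the figures in the table.

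**The case against.** **No error is shown.** An unadjusted comparison of randomised groups is legitimate. Its standard error already allows for chance imbalance, and the simulation shows its type I error held under independence. This stands. A reader might infer that the planned test is biased, or that imbalance makes its p-value wrong. The article does not support that: the shift exists only conditionally on an observed imbalance and averages out over randomisations.

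**The gain rests on assumptions.** The article supplies neither r nor d for state anxiety. The covariate and the outcome come from different instruments, and the outcome is taken just after a talk about an imminent invasive procedure, so r could be modest. The scripted contrast between arms is strong, so d could exceed 0.5. This also stands: at r = 0.3 the gain is about 4 points, and at alpha 0.05 a larger d leaves less to gain.

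**Adjustment does not repair the design.** A reader might take trait adjustment as a cure for imbalance in general. It corrects for one covariate only. Other differences between blocks remain, and the unit of allocation is still ignored.

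**Section 2.14.3 already permits control for trait anxiety.** It does, but only as exploration. The confirmatory estimate and p-value stay unadjusted.

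**It is only a secondary outcome.** True, and the primary conclusion is untouched. This limits the weight of the point but does not remove it.

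**Conclusion.** The point holds as a matter of efficiency. The plan fixes an unadjusted test for a confirmatory outcome while leaving a relevant pre-intervention covariate to exploratory work. At d = 0.5, 40 per arm, two-sided alpha 0.05 and independent patients, the power forgone is about 4, 12 and 19 points at r = 0.3, 0.5 and 0.6. These figures depend on assumed values of d and r, and block allocation makes the power levels optimistic. The planned test is neither biased over repeated randomisation nor anti-conservative on this account. The estimate is simply left uncorrected for any trait-anxiety imbalance that occurs. The allocation of whole blocks is a separate issue that this adjustment does not resolve.

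**What to change.** In section 2.14.2, make the confirmatory analysis of state anxiety a linear model of the t2 STAI-state total on group and the t1 STADI-Trait anxiety score. Report the adjusted mean difference with its 95% confidence interval, use the p-value for group in the Holm family, and keep the unadjusted t-test or Wilcoxon test as a sensitivity analysis.

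A permutation p-value should not be written in as a fallback for non-normal residuals. Permuting patients does not match the allocation. Permuting whole blocks gives 70 allocations with 4 blocks per arm (smallest two-sided p = 2/70 = 0.029) or 252 with 5 per arm (2/252 = 0.008), and neither can reach a first Holm step of 0.005.

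The model needs no new data and costs one degree of freedom and a short change of text. The real cost is procedural. The trial is preregistered and enrolment is described as having run from December 2023 to May 2024, so the change must be disclosed and documented as made before any group comparison was seen. If that cannot be shown, report the adjusted model as an additional analysis and leave the stated test as the confirmatory one.

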#### Exploratory analyses

2.14.3

The number needed to treat with optimized communication to prevent a certain level of headache-related impairment can be assessed exploratively (e.g., greater than 2 out of 10). Analyzing differences in reported side effects other than headache (assessed in the modified GASE questionnaire) allows us to test whether the optimized communication strategy influenced a wider range of side effect symptoms. Furthermore, the dataset lends itself to the exploration of associations between the study’s outcomes and demographic as well as baseline psychometric characteristics (e.g., age, sex, trait anxiety, trait depression), as their contribution to the outcomes can be controlled for and potential influences between outcomes, that is, through modulation, can be explored. The importance of perceived warmth and empathy of the physician—largely influenced by non-verbal communication—will be examined by analyzing the variance in side effect outcomes explained by patients’ ratings of the physician’s warmth, also probing for a potential modulatory influence on the group effect. The exploratory analyses are intended to make novel discoveries and help generate new hypotheses regarding biopsychosocial mechanisms through which the optimized communication might act or regarding predictive factors that might identify patients who benefit most from our optimized communication protocol.

## Discussion

3

This study investigates the cumulative impact of several communication strategies designed to reduce nocebo-related headaches after lumbar puncture. Our objective is to apply knowledge derived from preclinical research on expectation effects and their modifiers, testing the efficacy of easily implementable techniques to diminish the nocebo component of procedure-related unwanted effects in a naturalistic clinical setting.

The nocebo effect is arguably more prevalent and impactful in clinical settings than its better-studied positive counterpart, the placebo effect. Patients’ experiences with healthcare are often dominated by negative emotions due to their association with illness and disease. Anxiety about health, fear, helplessness, and discomfort are common, especially in hospitals, where patients undergo diagnostic procedures that are unpleasant (Walker et al., 2021). This negative environment fosters nocebo effects, which are fueled by anxiety and negative emotions (Benson et al., 2023). The impact of nocebo effects is substantial, leading both to direct suffering from symptoms and indirect consequences such as patients refusing or discontinuing necessary diagnostic procedures or treatments due to fear of negative outcomes (Colloca and Miller, 2011).

This study protocol provides detailed documentation of the applied communication techniques and outcome measures to inform other scientists and clinical experts aiming to develop strategies to mitigate nocebo effects. As LPs are a common and indispensable component of diagnostics in neurology, a substantial number of patients could benefit from such research efforts. Moreover, the use of the optimized communication strategies for LP could serve as a showcase for other medical procedures and their respective complications, and this study protocol can inform the design of future trials. A further strength of this study protocol lies in its immediate translational potential for improving patient care by illustrating simple measures that can be readily incorporated into daily clinical routines. Evidence supporting the efficacy of optimized communication may lay the foundation for best practices in the endeavor to mitigate nocebo effects in healthcare. Such best practices could serve as a crucial guide for physicians experiencing the dilemma that arises from the motivation to uphold patient autonomy in shared decision-making while avoiding unintended harm to their patients by disclosing risks and informing them about necessary procedures or treatments. Detailed study protocols like the present one can inform educational programs directed at, for example, medical or nursing students and professional healthcare providers, an effort that has already been initiated (Ohlmann et al., 2024; Westendorp et al., 2024). Looking ahead, strategies for multicenter trials and the use of digital communication could help to improve communication on a broader scale (Meijers et al., 2023; Ponten et al., 2024).

A key limitation of the study is that it was not tailored to provide detailed insights into the psychoneurobiological factors underlying the effects of optimized communication, which are necessary for a more nuanced mechanistic understanding. These will need to be addressed in follow-up studies and include, for example, the role of fear, interrogation of symptom-specificity in side effect expectations, and investigation of potential endocrinological and neuroactivity correlates. Furthermore, a more granular profile of the patient’s personality could help identify those that benefit most from communication-related techniques to reduce nocebo effects. The data collected here will allow us to explore the influence of anxiety, depression, and illness perception on expectations and side effects. However, other traits such as suggestibility, neuroticism, or optimism—which others have shown to correlate with nocebo effects—have not been assessed here (Corsi et al., 2016; Corsi and Colloca, 2017; Karacaoglu et al., 2023). As our optimized ICP protocol combines both verbal and non-verbal strategies in one group, it does not allow us to directly isolate the specific contribution of verbal communication techniques or assess the added benefit of incorporating warm and empathetic non-verbal cues. Ultimately, studies that disentangle the contributions of each element of optimized communication to side effect outcomes in clinical cohorts will help identify the most effective strategies for different patient groups or symptoms.

## Conclusion

4

This study protocol provides a comprehensive overview of the study design and intervention focused on enhancing communication during the informed consent process to reduce nocebo-related headaches. Conducting studies in real-world clinical environments is challenging but essential for translating insights from experimental nocebo studies into practical bedside applications. Our protocol is designed to serve as a guide for future studies.
